### Plans to promote participant retention and complete follow-up {18b}

Neurosurgical hematoma evacuation and endovascular MMA closure represent standard modalities both at the trial site and in the scientific community- the novelty of MEMBRANE is random assignment to surgery plus endovascular treatment versus surgery alone. Patients will deliberately be informed that trial participation guarantees no personal benefit whatsoever- however, it will also be explained there is scientific evidence that patients treated in a clinical trial environment may show superior outcomes compared to those managed under routine practice conditions.

Investigators, study nurses and other staff will take care of retaining participants until the scheduled last follow-up visits.

Patients who chose to discontinue participation, those who do not respond to multiple attempts of contact or cannot be reached by phone or mail will be considered losses to follow-up. Data will be recorded, stored, and used for final analysis unless participants actively demand data deletion. Those appeals will be handled by local data security officers in accordance with EU-GDPR.

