### Criteria for discontinuing or modifying allocated interventions {11b}

Patients may withdraw their consent at any time without providing a reason and thus terminate their participation in the study prematurely. Withdrawal from the study and reasons, if known, will be documented. Criteria for premature drop-out include:Subsequent occurrence of an exclusion criterionLoss of contactDeathDeclaration of withdrawn consent

Moreover, the principal investigator is entitled to terminate the study prematurely if:Patient recruitment remains inadequate despite multiple measures to improve enrolmentSerious problems with the quality of collected data cannot be resolvedUnforeseeable circumstances at the trial center prevent trial continuationUnacceptable risks arise (after a risk-benefit assessment by the Data Safety Monitoring Board)New scientific findings in favor of one or the treatment violate the equipoise principle

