### Sample size {14}

Because of the potential of notable morbidity, recurrent cSDH is considered both a clinically relevant and methodologically reliable, objective primary trial endpoint.

In one of the largest studies to date, Ban et al. compared a prospective series of 72 patients with cSDH undergoing MMA embolization with a historic standard-of-care group of 469 subjects. The overall risk difference (irrespective of hematoma evacuation) was estimated at 26% (95% CI 21 to 31%) in favor of endovascular management. There is much variability in reported cSDH recurrence risks with either treatment option, and unclarity about the realistic benefit of combined surgical and interventional therapy.

In view of the results of published studies (in particular Ban et al.), we conservatively presume recurrence rates of 30% in the control and 10% in the experimental arm during an observation period of 3 months.

Since our assumptions are subject to uncertainty, we will employ an adaptive design according to O’Brien-Fleming with one planned interim analysis to decide about the further trial progress, and to modify the target sample size if necessary and/or reasonable. For a power of 80% and a total alpha of 5%, data from 138 patients (i.e., 69 per group) are needed to detect a risk difference of 20% by a *z*-test for independent samples. Assuming a drop-out and lost-to-follow-up rate of 10%, we plan to enroll 154 patients (i.e., 77 per treatment arm) unless the interim look prompts any adjustment.

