## Statistical methods

### Statistical methods for primary and secondary outcomes {20a}

The primary outcome, i.e., reduction in cSDH recurrence through the experimental, surgical plus endovascular treatment, compared to surgery alone, will be analyzed using a chi-square fourfold test for independent samples. The two-sided significance level *α* is set at 5% and the power at 80%. Superiority of the experimental intervention over control is assumed, if the resulting *p*-value is below the nominal significance level of 0.00031 at the time of interim analysis (prompting early trial termination), or the nominal significance level of 0.0469 at the time of final analysis.

Secondary categorical outcomes will be investigated by the Cochran-Mantel-Haenszel (CMH), chi-square, or Fisher’s exact test (if one of the cell frequencies is <5). Recurrence-associated complications, complications associated with endovascular embolization, and (serious) adverse events will be expressed as absolute and relative frequencies.

Exploratory analyses will be performed for the distribution of genetic variants and their correlation (by Pearson’s *phi*-coefficient) with factor XIII deficiency (<70%) across the entire cohort without stratification for the type of intervention. The closer the *phi*-coefficient to 1 or -1, the stronger the association (or predisposition) between genetic variants and factor XIII deficiency. Advanced analyses will be performed to study the association between heterozygous, homozygous, and wild type variants, factor XIII activity, and cSDH recurrence.

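### Stopping visits, loss of contact and withdrawal all end as drop-out or loss to follow-up, and the primary set requires the 3-month visit, so some knowable re-operations and deaths may be lost

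*Protocol article*

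**What the plan says.** Four sections of the protocol article bear on this.

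- **Retention {18b}** puts three kinds of patient into one class, losses to follow-up: "Patients who chose to discontinue participation, those who do not respond to multiple attempts of contact or cannot be reached by phone or mail". It then says that data are recorded and used in the final analysis unless the patient asks for deletion.
- **Discontinuation {11b}** says that patients who withdraw consent "thus terminate their participation in the study prematurely". Its list of drop-out criteria puts loss of contact, death, withdrawn consent and a later exclusion criterion side by side.
- **Outcomes {12}** defines recurrence by either of two criteria, haematoma volume or a recurrence that needs surgery. Either one is enough. The mRS gives death the value 6.
- **Non-adherence and missing data {20c}** analyses patients as randomized, but requires outcomes to be fully documented at the 3-month visit. It adds a missing-data analysis, sensitivity analyses and, if suitable, multiple imputation.

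The allowance for losses is in Sample size {14}: "Assuming a drop-out and lost-to-follow-up rate of 10%, we plan to enroll 154 patients".

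**The concern.** Embolization is the only study intervention ({11c}) and takes place within 72 h of surgery ({13}). A patient who stops after that has no study treatment left to stop and is only ceasing to attend. Such a patient may be quite willing to have a re-operation or vital status looked up. Sections {11b} and {18b} provide no category for this.

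Together with {20c}, the visit becomes the way into the primary analysis. A patient re-operated for recurrence at six weeks who then does not return has met the endpoint, but by the wording of {20c} is outside the primary set. A patient who dies is listed as drop-out although the mRS has a value for death.

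The risk is mainly bias. Patients know their treatment ({17a}), so reasons for not returning can differ by arm and can relate to outcome: too disabled to travel, treated elsewhere, or well and uninterested. The direction cannot be predicted. Enrolling more patients protects power but does not correct selection.

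**Working it through.** **Inputs.** Sample size {14} gives 138 evaluable patients (69 per arm), 154 enrolled (77 per arm), a 10% loss allowance, and rates as follows: "we conservatively presume recurrence rates of 30% in the control and 10% in the experimental arm".

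**1. The plan's own figure.** 138 / (1 − 0.10) = 153.3, rounded up to 154; per arm 69 / 0.90 = 76.7, rounded up to 77. This reproduces exactly. (A plain pooled z-test needs 62 per arm, so 69 is on the large side; nothing here depends on that.)

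**2. Size of the allowance.** 154 − 138 = 16 patients, 8 per arm; 16 / 154 = 10.4%.

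**3. Recurrences expected among them at the planned rates.** 8 × 0.30 + 8 × 0.10 = 2.4 + 0.8 = 3.2.

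**4. Extreme-case bounds.** Observed events: 69 × 0.30 = 20.7, taken as 21; 69 × 0.10 = 6.9, taken as 7.

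| Fate of the 8 missing per arm | Control | Experimental | Difference |
|---|---|---|---|
| None recur in control, all in experimental | 21/77 = 27.3% | 15/77 = 19.5% | 7.8 points |
| All recur in control, none in experimental | 29/77 = 37.7% | 7/77 = 9.1% | 28.6 points |

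Without rounding the counts, the range is 5.8/77 = 7.5 to 21.8/77 = 28.3 points.

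**5. Power.** For the pooled z-test, power = Φ[(0.20√n − z√(2 × 0.20 × 0.80)) / √(0.30 × 0.70 + 0.10 × 0.90)]. At two-sided 0.05 (z = 1.96), n = 69 gives 84.3% and n = 77 gives 88.1%. At the final nominal level of 0.0469 the figures are 83.7% and 87.5%. Recovering every outcome would add about 4 points, so power is not the main issue.

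**6. What records can supply.**

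| Status of the non-attender | Primary outcome | mRS |
|---|---|---|
| Re-operated for recurrence | Event, settled | Missing |
| Died, no re-operation | Not settled; death is not a component | 6 |
| Alive, no re-operation, no CT | Not settled; the volume criterion needs imaging | Missing |

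**7. Why the third row must not be left out of the analysis.** Suppose, as an assumption, that all 3.2 recurrences in step 3 are re-operations and are recovered, while the other non-attenders are simply dropped. Control becomes (20.7 + 2.4) / (69 + 2.4) = 32.4% and experimental (6.9 + 0.8) / (69 + 0.8) = 11.0%. Both exceed the planned rates, and the difference becomes 21.3 points instead of 20. Adding only events inflates recurrence. Counting all the others as recurrence-free would err the other way by missing recurrences that meet only the volume criterion.

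**The case against.** A reader might infer that collection ceases once a patient stops, and that about 10% of primary outcomes are thrown away needlessly. The documents do not support either statement.

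- **Collection is not forbidden.** {18b} says that data are recorded and used unless deletion is demanded; whether this reaches data arising after discontinuation is unclear. {22} requires serious adverse events in the study period to be documented, and a fatal event or a hospital admission qualifies. This stands, with a limit: {22} covers events that a participant reports or an investigator observes, which may miss a non-attender treated elsewhere. An adverse event entry also does not bring the patient into the set defined in {20c}.
- **The 10% is a planning allowance.** It combines drop-out and loss to follow-up, is already absorbed by the enrolment target, and includes deaths and withdrawn consent. For some of these patients further collection is impossible or not permitted. No figure for the recoverable share is given. This stands.
- **Records settle only part of the endpoint.** They can prove a surgical recurrence but not the absence of recurrence, and death is not a primary component. This stands and shapes the fix.
- **The bounds are generic.** Any trial with 8 of 77 missing per arm and these counts would have them. This stands; they limit the possible bias and do not estimate it.
- **The article is condensed.** A record check may be described in the full protocol or consent form, neither of which is shown, so its absence here is not an error in itself. What remains is stated text: the grouping in {18b}, death as drop-out in {11b}, and the visit requirement in {20c}.
- **Missing data are addressed.** {20c} foresees sensitivity analyses and perhaps imputation. These are useful for what cannot be known, but are a weak substitute for a re-operation that can be looked up.

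**Conclusion.** The point holds in a limited form. Followed as written, {11b}, {18b} and {20c} can remove from the primary analysis a re-operation that alone meets the endpoint, and can class a death as attrition although the mRS scores it. The loss may differ by arm because patients are unblinded.

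The size is uncertain. The allowance is 16 patients, with about 3.2 recurrences among them if the planned rates apply to non-attenders too. How many were re-operated, and how many could be traced, is unknown. The range of 7.8 to 28.6 points assumes 8 missing per arm and opposite extremes in the two arms; the true bias is very probably much smaller. The change is worth making because it is cheap and because permission to consult records cannot readily be obtained later from patients who are out of contact.

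**What to change.** 1. In {11b}, {18b} and the consent form, distinguish (a) stopping visits, with re-operation and vital status at 3 months still obtained from hospital records or the treating physician, from (b) full withdrawal of consent to data collection. Place non-responders under (a), within what the consent allows.
2. Do a record check for every patient under (a) without a 3-month visit, in both arms alike, once the visit window has closed.
3. Amend {20c} so that a documented re-operation for recurrence within 3 months counts as a primary event without the visit. The record check has no effect on the primary analysis unless this is changed.
4. Score death as mRS 6 and stop listing it simply as drop-out.
5. Keep patients with no recorded re-operation and no CT as missing on the volume criterion, and handle them by the multiple imputation or sensitivity analyses foreseen in {20c}. These should be made firm for this group. Do not count such patients as recurrence-free.

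The cost is protocol and consent wording, plus a record check or call for about 16 patients if losses match the allowance. The volume criterion stays incompletely ascertained for them. If the full protocol already provides such a check, only the wording of these sections needs to be aligned.

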### Data management {19}

Electronic case report forms (eCRF) will be computed in secuTrial® (interActive Systems Berlin, Germany). The system fully complies with ICH-GCP and FDA 21 CFR Part 1, is hosted by the Center for Clinical Research at the trial institution and was successfully used for data storage, exchange, and processing in multiple clinical trials and observational studies. Dedicated data managers are responsible for programming eCRFs and quality maintenance.

Investigators and trial staff will be introduced to the platform and trained in data entry during the initial kick-off meeting prior to recruitment of the first patient.

Only authorized clinical investigators and trial personnel will be granted access to the study database by a personal ID. Depending on their role within the study, users will be assigned tailored authorizations to the respective forms.

All study data are stored and processed in a pseudonymized fashion. For data transmission between the ward and peripheral computers and the study database, a 128-bit SSL connection is used for data encryption to avoid manipulation. Each time data is entered into secuTrial®, an audit trail is created which guarantees complete versioning and traceability of changes. Customized field properties, rules, and checks in secuTrial®, which indicate the input of implausible values, inconsistent information, or the lack of mandatory information, help to optimize data quality. Once data entry is complete, the database will be closed and data exported for statistical analysis.

### Confidentiality {27}

secuTrial® uses a pseudonymization concept that completely separates personal from identifying and medical data. When adding a new patient to the database, identifying data are entered on a form which is only printed but not saved on the server. On this form, the so-called participant identification list, a pseudonym consisting of a combination of six alphanumeric characters is automatically created for each patient. The form is kept in a locked space to which only the principal investigator has access and may be used to unblind personal data if necessary.

### Plans for collection, laboratory evaluation, and storage of biological specimens for genetic or molecular analysis in this trial/future use {33}

Blood drawn from patients at baseline will routinely be analyzed for platelet count, activated partial thromboplastin time (aPTT), and fibrinogen concentration. For study purposes, we will analyze factor XIII concentration by means of STA-R (Stago, Düsseldorf, Germany) with HEXAMATE Factor XIII (Roche Diagnostics, Basel, Switzerland), and the presence of genetic variants F13A1 rs2815822, F13B rs12134960, F13A1 rs2815822 (C > A) and F13B rs12134960 (C > G). To determine factor XIII activity, blood samples will be cryopreserved for later analysis.

## Statistical methods

### Statistical methods for primary and secondary outcomes {20a}

The primary outcome, i.e., reduction in cSDH recurrence through the experimental, surgical plus endovascular treatment, compared to surgery alone, will be analyzed using a chi-square fourfold test for independent samples. The two-sided significance level *α* is set at 5% and the power at 80%. Superiority of the experimental intervention over control is assumed, if the resulting *p*-value is below the nominal significance level of 0.00031 at the time of interim analysis (prompting early trial termination), or the nominal significance level of 0.0469 at the time of final analysis.

Secondary categorical outcomes will be investigated by the Cochran-Mantel-Haenszel (CMH), chi-square, or Fisher’s exact test (if one of the cell frequencies is <5). Recurrence-associated complications, complications associated with endovascular embolization, and (serious) adverse events will be expressed as absolute and relative frequencies.

Exploratory analyses will be performed for the distribution of genetic variants and their correlation (by Pearson’s *phi*-coefficient) with factor XIII deficiency (<70%) across the entire cohort without stratification for the type of intervention. The closer the *phi*-coefficient to 1 or -1, the stronger the association (or predisposition) between genetic variants and factor XIII deficiency. Advanced analyses will be performed to study the association between heterozygous, homozygous, and wild type variants, factor XIII activity, and cSDH recurrence.

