**Assessments**						
Demographics, medical history, laboratory data			X			
Neurological tests			X		X	X
Computed tomography			X		X	X
Complications				X	X	X

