## Data collection and management

### Plans for assessment and collection of outcomes {18a}

Data will be entered by clinical investigators and supporting trial personnel on electronic case report forms (eCRFs) created by secuTrial®.

Neurological examination comprises the modified Rankin scale for neurologic disability [36], the muscle function according to Janda [37], the presence of word finding disorders, hemiparesis, and anisocoria, as well as vigilance. Standard laboratory parameters will be taken from peripheral blood at baseline and during follow-up. The size and extent of cSDH will be measured on non-contrast CT scans.

The following parameters of recurrence-associated or intervention-associated complications will be documented for study purposes:

Recurrence-associated:Cerebral edemaCerebral infarction

Intervention-associated:Dissection of vessels by the guide wireDislocation of particles or coilsIschemia caused by internal-external vascular connectionsRetinal blindnessEpidural hematoma after MMA perforationInflammation or abscess at the puncture siteVascular fistula at the puncture siteVascular bulging at the puncture siteAllergic reaction to the contrast agentAcute renal failure

Complications not covered by predefined categories may be entered as free text in the eCRF.

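### The primary chi-square is valid and meets its power target, but it leaves unused the baseline haematoma volume that the trial already measures; adjustment could gain a little efficiency

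*Protocol article*

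**What the plan says.** The article's section on statistical methods for primary and secondary outcomes {20a} says that the primary outcome "will be analyzed using a chi-square fourfold test for independent samples". The level is two-sided, with a "nominal significance level of 0.0469 at the time of final analysis". The interim section {21b} relies on the same test. Neither section names a covariate.

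The primary outcome section {12} counts a recurrence if the haematoma regrows to about its baseline volume or if it needs surgery. Baseline volume is therefore the reference for the first criterion only. The section on outcome collection {18a} adds: "The size and extent of cSDH will be measured on non-contrast CT scans". Table 1 schedules CT at t1, t3 and t4, and lists "Demographics, medical history, laboratory data" at t1. Age appears in the analysis only as a split at 67 years, in the additional analyses {20b}.

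The sample size section {14} assumes "recurrence rates of 30% in the control and 10% in the experimental arm" and states that "data from 138 patients (i.e., 69 per group) are needed to detect a risk difference of 20" percent.

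**The concern.** A baseline measurement that helps predict the outcome explains part of the chance variation between arms. A plain fourfold table cannot use it. Few events are expected here (about 28 at the final analysis), so chance imbalance in a prognostic covariate could noticeably shift the estimated risk difference. The interim estimate, from 69 evaluable patients, also guides decisions on sample size and futility, so its precision matters. If volume predicts recurrence, adjustment would give somewhat more power at no cost in recruitment.

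**Working it through.** **1. The plan's own sample size.** Inputs from {14} and {20a}: risks 0.30 and 0.10, difference 0.20, power 80%, two-sided alpha 5%, 1:1 allocation.

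- Unpooled z-test: n = (1.960 + 0.842)² × (0.21 + 0.09) / 0.20² = 58.87 per arm.
- With continuity correction: (n/4) × [1 + √(1 + 4/(0.20n))]² = 14.72 × (1 + 1.157)² = 68.5, so 69 per arm and 138 in total.
- Drop-out: 138/0.9 = 153.3, so 154.

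Both stated figures reproduce by this route.

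**2. Power of the planned test with 69 per arm.** For the uncorrected chi-square with mean risk 0.20:

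power = Φ{[0.20√69 − z × √(2 × 0.20 × 0.80)] / √(0.21 + 0.09)}

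- At 0.05, z = 1.960: Φ[(1.661 − 1.109)/0.548] = 84.3%.
- At 0.0469, z = 1.987: Φ[(1.661 − 1.124)/0.548] = 83.7%.

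The target of 80% is met without adjustment.

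**3. Expected events.** Final: 69 × 0.30 + 69 × 0.10 = 27.6, about 28. Interim, with 69 evaluable in total: 69 × 0.20 = 13.8, about 14.

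**4. What adjustment might add.** The prognostic strength of volume is not in the article, so it is assumed, expressed as the AUC of volume for recurrence in the control arm. Simulation: 69 per arm, marginal risks 30% and 10%, two-sided level 0.0469, a standard normal covariate for log volume, and one uninformative second covariate standing in for age.

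| Assumed AUC | Chi-square | Adjusted | Difference (points) |
|---|---|---|---|
| 0.50 | 85.6% | 84.9% | −0.7 |
| about 0.63 | 86.0% | 86.5% | +0.5 |
| about 0.70 | 85.4% | 88.0% | +2.6 |
| about 0.78 | 84.6% | 90.1% | +5.5 |

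The true chi-square power is the same in every row; its spread is simulation error, roughly half a point per entry. A separate simulation adjusting for volume alone gave similar gains: 84.4% to 86.1%, 85.7% to 88.4% and 85.8% to 91.1% at AUC 0.63, 0.70 and 0.78. The variance of the standardised risk difference, relative to the raw one, was 0.97, 0.93 and 0.83.

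**5. Type I error.** With 20% in both arms, the two-covariate adjusted test rejected in 4.9% to 5.5% of runs at the nominal 4.69%, a slight excess at most. At an interim level of 0.0031 it rejected in about 0.3%, so the small number of events at that look did no visible harm. The article prints the interim level as 0.0031 in {21b} and 0.00031 in {20a}. That is a separate matter; only 0.0031 was checked here.

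**6. More covariates.** Volume, an uninformative second covariate and two uninformative binary strata together gave 86.7% versus 85.3% (no prognosis), 84.4% versus 85.0% (AUC about 0.63) and 85.2% versus 87.1% (about 0.70). The cost of a wrong guess rises to 1.4 points and the gain stays under 2, which argues for a short list.

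**The case against.** The case for leaving the test alone is strong. The chi-square is valid under randomisation, agrees with the z-test behind the sample size, and exceeds its power target. Randomisation is stratified to balance key baseline characteristics {16a}; the factors are not named, so age or size may be among them. An analysis plan that is not shown may already hold an adjusted supportive analysis. All of this stands, and it is why the point is optional.

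Three stronger readings are tempting, and the article supports none of them.

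- A reader might infer that the primary test is wrong or the trial underpowered because volume is ignored. Step 2 shows otherwise.
- A reader might infer that volume must be prognostic because it defines criterion 1. A larger baseline makes regrowth to that size harder, but may make reoperation under criterion 2 more likely, so even the net direction is open. The background section lists older age as a risk factor for having the condition, not for recurrence.
- A reader might assume a correlation of about 0.5 and claim some 8 points of power. That value has no basis in the article. It would imply an odds ratio of about 5 per standard deviation (AUC 0.83).

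What remains is that the confirmatory test is fixed in this document as unadjusted, while a natural candidate covariate is already being measured.

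**Conclusion.** The point holds as a modest gain in efficiency, of low priority and with low confidence about its size. Under the protocol's own risks, adjustment for volume and age would change power by between a loss of under 1 point (no prognosis) and a gain of about 5 points (control-arm AUC about 0.78). For a weak to moderate predictor the gain is about 0.5 to 3 points. These figures rest on an assumed prognostic strength, a covariate that acts linearly on the log-odds scale, and complete data on 69 patients per arm. They do not show bias, inflated error or a missed power target in the current plan.

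**What to change.** In {20a}, before any outcome is seen, make the primary test a logistic-regression score test for treatment with two covariates: log haematoma volume and continuous age. Report the risk difference standardised over the observed covariates with its 95% CI, and keep the unadjusted chi-square as a sensitivity analysis. Apply the same choice in {21b}.

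Three details need fixing in the wording:

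- **Which scan.** Volume should come from the qualifying pre-operative scan made before randomisation. The participant timeline {13} and Table 1 list the baseline visit (t1) after randomisation (t0), so naming the t1 CT would leave the covariate's timing open.
- **Bilateral haematomas and MRI.** Bihemispherical disease and detection by MRI are both allowed at entry {10}, so state how volume is defined in each case.
- **Number of covariates.** Keep to these two, given about 28 events at the final analysis and about 14 at the interim.

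The cost is a paragraph of text and no extra patients. The downside is that a model replaces a fourfold table, and up to about 1 point of power is lost if neither covariate is prognostic. If the sponsor prefers to keep the chi-square as primary, the adjusted standardised risk difference can be pre-specified as a key supportive analysis; that improves the estimate but not the power of the confirmatory test.

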## Assignment of interventions: allocation

### Sequence generation {16a}

Patients will randomly be assigned to trial arms using a web platform and an extended stratified block algorithm. The algorithm guarantees even distribution of key baseline characteristics across the intervention and the control group.

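### Allocation is stratified but the primary test is an unstratified chi-square, which forgoes some power if the strata predict recurrence

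*Protocol article*

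**What the plan says.** On allocation, the Protocol article, Sequence generation {16a}, states: "Patients will randomly be assigned to trial arms using a web platform and an extended stratified block algorithm". It adds: "The algorithm guarantees even distribution of key baseline characteristics across the intervention and the control group". Implementation {16c} again refers to stratified blocks. Neither section names the factors.

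On analysis, Statistical methods {20a} says the primary outcome "will be analyzed using a chi-square fourfold test for independent samples". Its success criterion is a p-value below the interim level "or the nominal significance level of 0.0469 at the time of final analysis". Interim analyses {21b} bases early stopping on the same chi-square. CMH is named only further down {20a}: "Secondary categorical outcomes will be investigated by the Cochran-Mantel-Haenszel (CMH), chi-square".

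On planning, Sample size {14} states: "we conservatively presume recurrence rates of 30% in the control and 10% in the experimental arm during an observation period of 3 months". It concludes: "data from 138 patients (i.e., 69 per group) are needed to detect a risk difference of 20% by a *z*-test for independent samples".

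Methods for additional analyses {20b} splits primary and secondary outcomes by age at 67 years. It does not say that age is a randomisation stratum, and it does not change the primary test.

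**The concern.** Balancing the arms on a factor that predicts recurrence removes part of the chance variation between them. The plain chi-square still counts that variation in its variance. Its p-value is then somewhat too large and a matching interval for the risk difference somewhat too wide. A test that conditions on the strata recovers the difference.

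What is at stake is efficiency in a trial of 138 evaluable patients. It matters most if the true effect is smaller than planned, a possibility that Interim analyses {21b} itself provides for, and at the early look, where the same test decides stopping. The point concerns a test that the protocol fixes, not a detail left open: an analysis plan that used CMH for the primary comparison would contradict {20a}.

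**Working it through.** **Inputs from the protocol.** 69 evaluable patients per arm, 1:1 allocation, recurrence 30% vs 10%, two-sided final level 0.0469.

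**Assumptions, because the factors are not named.** Two equal strata, allocation balanced within each, a common odds ratio, and an overall control risk of 30%. The stratum control risks range from 30/30% (no prognostic value) to 10/50%.

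**1. The plan's sample size.** An unpooled z-test at 5% two-sided and 80% power gives n = (1.960 + 0.842)² × (0.30×0.70 + 0.10×0.90) / 0.20² = 7.849 × 0.30 / 0.04 = 58.87 per arm. The continuity correction, (n/4) × [1 + √(1 + 4/(0.20n))]², gives 68.50, so 69 per arm and 138 in total. Dropout: 138/0.9 = 153.3, so 154. Both stated figures reproduce, for an unstratified test. At 69 per arm and level 0.0469, the uncorrected chi-square has 83.7% power by formula and 85.5% by exact enumeration.

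**2. Type I error by formula.** With no treatment effect, the ratio of the true to the assumed variance is the mean of p(1−p) over strata, divided by 0.30×0.70 = 0.21. The critical value is 1.987, so the true level is 2 × P(Z > 1.987/√ratio).
- 20/40%: mean (0.16 + 0.24)/2 = 0.200, ratio 0.952, level 4.2%.
- 15/45%: mean (0.1275 + 0.2475)/2 = 0.1875, ratio 0.893, level 3.5%.
- 10/50%: mean (0.09 + 0.25)/2 = 0.170, ratio 0.810, level 2.7%.

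**3. Simulation** (200,000 trials per scenario, 69 per arm, level 0.0469, stratum sizes varying at random):

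| Stratum control risks | Type I error, chi-square | Type I error, CMH | Power at 30% vs 10%, chi-square | Power at 30% vs 10%, CMH |
|---|---|---|---|---|
| 30/30% | 4.7% | 4.6% | 85.2% | 84.7% |
| 25/35% | 4.6% | 4.7% | 85.4% | 85.2% |
| 20/40% | 4.2% | 4.7% | 85.6% | 85.9% |
| 15/45% | 3.6% | 4.7% | 86.1% | 87.4% |
| 10/50% | 2.8% | 4.7% | 86.8% | 89.2% |

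The Monte Carlo standard error of a power figure is about √(0.85×0.15/200,000), or 0.08 points. With stratum sizes held fixed, the CMH gains in the last three rows are about 0.2, 1.2 and 2.3 points. The loss at 30/30% is then about 0.7 to 0.8 points instead of 0.5.

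**4. A smaller true effect.** At 30% vs 16% (an assumption), chi-square power is only about 49%. CMH gains about 1.3, 3.3 and 6.4 points for 20/40%, 15/45% and 10/50%.

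**5. The interim look.** This uses 35 per arm, 30% vs 10%, and the level 0.0031 printed in {21b}. ({20a} prints 0.00031; that conflict is a separate matter.) With 17 low-risk and 18 high-risk patients per arm, the chance of crossing rises from 17.4 to 18.6%, from 17.0 to 20.4% and from 16.5 to 22.5%. If the strata are not prognostic, CMH loses about 1 point. With so few patients these figures depend on the exact counts. At 17 per stratum and arm, a re-run gave changes of −0.8, +0.9 and +3.3 points, and −2.3 points with non-prognostic strata. They are indicative only.

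**The case against.** The strongest reply is that nothing promised is lost. The trial was sized for an unstratified z-test and is analysed with the equivalent chi-square. That test exceeds 80% power under the planning assumptions and never exceeds its nominal level because of the stratification. All of that stands.

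The benefit is also conditional. At 25/35% the two tests are practically equal, with chi-square slightly ahead. At 20/40%, a doubling of risk between strata, CMH gains only 0.2 to 0.3 points at 30% vs 10%. Gains above 1 point there need a three- to five-fold difference in risk between strata, and the protocol gives no evidence of one. A reader might infer that the chi-square is necessarily conservative and loses power. The document does not support that, since it names no strata. It calls the balanced characteristics key ones, which makes some prognostic value a reasonable expectation but no more.

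Nor is CMH free of cost: it loses a fraction of a point at the final analysis if the strata do not matter. At the interim, about 69 × 0.20 = 14 events are expected, so many small strata would be a practical difficulty.

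Two replies do not dispose of the point. The age split in {20b} is an additional analysis and leaves the primary test unstratified. And although the list of strata may well sit in an analysis plan that is not shown, the choice of primary test is made in the protocol.

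**Conclusion.** The mismatch is in the text, and its direction is clear: if the strata predict recurrence, the planned test is conservative. Under the two-stratum assumption its final-analysis type I error falls from 4.69% to about 4.2 to 4.3%, 3.6% or 2.8% as the strata strengthen. The power forgone runs from about 0.2 to 2.3 points at the planned effect and from about 1.3 to 6.4 points at 30% vs 16%.

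A reader might conclude that the trial is underpowered or that its error rate is wrong. Neither follows: the 80% power at 30% vs 10% is kept, and the error bound is respected at both looks. It is an efficiency point of modest size, and it rests on the prognostic strength of factors that the document does not name.

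**What to change.** Name the randomisation strata. Make the primary test at interim and final a CMH test stratified by them, reported with a Mantel-Haenszel common risk difference and 95% CI. Pre-specify how strata with few patients or events are pooled, with the interim in mind. Keep the unstratified chi-square as a sensitivity analysis. Fix all of this before any outcome data are seen, because a later choice between the two tests would be open to the charge of being data-driven.

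The cost is wording in {20a} and {21b} and in the analysis plan. Allocation runs through the same electronic system that captures the data, so the stratum values should already be on file. No extra patients are needed. The statistical price, if the strata turn out not to be prognostic, is about 0.5 to 0.8 points of power at the final analysis and about 1 point at the interim with 35 per arm (2.3 points in the check with 34 per arm).
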